### Statistical analysis

Data entry will be performed by two independent researchers so that the accuracy of the input data can be cross-checked. The Statistical Package for Social Sciences (SPSS) version 26 will be used to conduct the data analysis. Intention-to-treat analysis will be performed. The normality of the data will be checked using the Shapiro–Wilk test. To compare the baseline characteristics of the four groups, one-way ANOVA (or its nonparametric equivalent: Kruskal–Wallis test) or Chi-square tests will be used, depending on whether the criteria for parametric statistics are fulfilled. Those relevant variables that show important between-group differences will be entered as covariates for subsequent analysis. To compare the treatment effects of the 4 intervention approaches, multivariate 4 × 3 ANOVA or ANCOVA with repeated measures (mixed design; repeated factor: time; between-subject factor: group) will be used to determine the time effect and treatment × time interaction effect for each outcome variable of interest. The Greenhouse–Geisser correction will be applied if the assumption of sphericity is violated. If significant results are found, *post-hoc* multiple comparisons of group effects and contrast analyses of time effects will be performed. Bonferroni adjustment will be performed in *post-hoc* analysis to account for the increased risk of Type I errors associated with multiple comparisons. If the criteria for parametric statistics are not fulfilled, the Mann–Whitney test and Wilcoxon test will be used.

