### Outcome measures

All demographic information (e.g., age, gender and affected side, etc.) will be collected at baseline assessment session. All outcome assessments will be performed by a blinded assessor in each hospital on three occasions, i.e., at baseline, within 1-week after the completion of intervention, and at a 4-week follow-up.

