### Sample size

GPower 3.1 software (Heinrich-Heine-Universitat, Dusseldorf, Germany) was used to estimate the sample size. Wang et al. (36) 8-week traditional Chinese herbs hot compress (TCHHC) trial demonstrated a significant interaction on the total WOMAC score between the TCHHC combined with therapeutic exercise group and the therapeutic exercise alone group, yielding a partial eta-squared (
$\eta_{p}^{2}$
) of 0.148, corresponding to an effect size of *f* = 0.416 (36). A conservative approach was adopted for our sample size estimation, considering the comparison of two distinct treatment factors—ECHT and PEMF—and their combined application, alongside a reduced intervention duration of 4 weeks. Employing a 4 (group factor) × 3 (time factor) RM ANOVA framework, and assuming a small effect size (*f* = 0.15), a significance level (*α*) of 0.05, statistical power of 0.80, and accounting for a 15% attrition rate, the total sample size required was 124 participants, evenly distributed across the four groups, i.e., 31 in each group. The sample size is expanded by 10% compared to the original registration in the Chinese Clinical Trial Registry. This modification was necessitated by a post-initiation adjustment to the attrition rate assumption, which was revised upward to a more conservative 15% based on emerging data from the ongoing trial.

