### Withdrawal and adverse events

All the intervention methods in this trial are very safe, however, if participants show irreversible intervention-related adverse events during the trial, such as nausea, dizziness, disorientation, or fatigue, the trial will be stopped by the participant and registered. Moreover, this study will strictly comply with the clinical operation and internationally recognized legal requirements. Any adverse events will be reported directly to the ethics committee immediately, and the intervention regimen will be adjusted accordingly after each adverse event. There is no anticipated harm or compensation for trial participation. In addition, the following measures will be undertaken to achieve the best intervention environment: (1) during the 4-week intervention, an individualized intervention plan will be made for each participant on a weekly basis, and the intervention schedule will be adjusted according to the actual conditions of the participant; (2) close attention will be paid and regular feedback will be given to the participants during intervention; (3) the intervention effect on participants during the intervention will be evaluated weekly; and (4) participants’ decision to withdraw from the study will be supported.

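### The plan promises intention-to-treat, but the repeated-measures ANOVA it names keeps, by itself, only participants with all three visits

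*Protocol article*

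**What the plan says.** All places are in the protocol article.

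- **Statistical analysis, population:** "Intention-to-treat analysis will be performed".
- **Statistical analysis, method:** to compare the four approaches, a 4 × 3 "ANOVA or ANCOVA with repeated measures (mixed design; repeated factor: time; between-subject factor: group) will be used" for each outcome. Also: "The Greenhouse–Geisser correction will be applied if the assumption of sphericity is violated".
- **Statistical analysis, software:** "The Statistical Package for Social Sciences (SPSS) version 26 will be used to conduct the data analysis". Rank tests are the fallback, but what triggers them is failure of the parametric criteria, not missing visits.
- **Outcome measures:** assessments take place "at baseline, within 1-week after the completion of intervention, and at a 4-week follow-up".
- **Sample size:** "accounting for a 15% attrition rate, the total sample size required was 124 participants", which is 31 per group. The 15% was raised after the trial started, in light of data from the running trial.
- **Withdrawal and adverse events:** after irreversible intervention-related adverse events, "the trial will be stopped by the participant and registered". The same section says that the regimen is adjusted after each adverse event.

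**The concern.** The stated population and the stated method do not fit together. Intention-to-treat means that everyone randomised is analysed in the allocated group. Classical repeated-measures ANOVA needs a complete row of baseline, post-intervention and follow-up values for each participant, and SPSS deletes incomplete rows. A participant measured straight after treatment who misses only the follow-up is therefore lost from the post-intervention comparison as well.

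What is at stake is the randomised comparison. Completers are a subset selected after randomisation. If those who leave differ in outcome from those who stay, and the arms differ in how many or which participants leave, the contrast is biased. Two features make this possible here:

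- Participants know their treatment, since blinding covers only the assessors and the analyst, and both primary outcomes (VAS and WOMAC) are self-reported.
- Burden is unequal. Two arms wear a herbal dressing for 6–8 h on treatment days, while the control arm has 30 minutes of health education after exercise.

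**Working it through.** **1. Which method is meant.** The section describes a mixed design with time as repeated factor and group as between-subject factor, plus a Greenhouse–Geisser correction. That is a split-plot ANOVA. A likelihood-based mixed model models the covariance directly and has no Greenhouse–Geisser step. The section also uses the word multivariate, but the multivariate form of the repeated-measures test needs complete records too.

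**2. Reproducing the plan's 124.** The article gives k = 4 groups, m = 3 times, f = 0.15, α = 0.05, power 0.80 and attrition 15%. It does not give the correlation between visits (ρ) or the sphericity parameter (ε). I assume ρ = 0.5 and ε = 1, the values that reproduce the figure for the group × time interaction.

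- λ = f² × N × m × ε / (1 − ρ) = 0.0225 × 105 × 3 / 0.5 = 14.175
- df1 = (k − 1)(m − 1)ε = 6; df2 = (N − k)(m − 1)ε = 101 × 2 = 202
- Power is 0.799 at N = 104 and 0.804 at N = 105, so the smallest N is 105.
- 105 / (1 − 0.15) = 123.5, rounded up to 124. This matches.

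The match depends on ρ: the same steps give 148 at ρ = 0.4 and 99 at ρ = 0.6.

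**3. Expected loss.** This uses only the stated 124 and 15%, not ρ or ε.

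- 124 × 0.15 = 18.6, about 19 participants
- Per arm, if spread evenly: 31 × 0.15 = 4.65, so 4 to 5
- Left with complete records: 124 × 0.85 = 105.4, about 105

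**4. Power.** Under the assumptions of step 2, power is 0.804 at 105. It would be 0.877 at 124 only if nothing were missing, so 0.877 is an upper bound for any method that keeps everyone.

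**5. Possible bias, with assumed inputs.** Let d be the dropout proportion in an arm, and let δ be the mean outcome of dropouts minus that of completers, taken as equal in both arms. The completer mean differs from the full-arm mean by d × δ, so the contrast between two arms is shifted by |d₁ − d₂| × δ. For δ I use 1.8 points, the minimum important difference that the article cites for the numeric pain scale.

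| Dropout in two arms (assumed; average 15%) | Shift in pain contrast |
|---|---|
| 15% and 15% | 0 |
| 20% and 10% | 0.10 × 1.8 = 0.18 |
| 25% and 5% | 0.20 × 1.8 = 0.36 |

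The last value is a fifth of 1.8. The article gives no dropout by arm, so the table shows scale only. It is not a forecast.

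**The case against.** The strongest reply is that intention-to-treat and repeated-measures ANOVA are compatible if missing values are imputed first. The article never mentions completers or listwise deletion. It condenses a fuller protocol, and an analysis plan that is not shown may deal with missing data. This stands in part. It would be wrong to infer that the named method can never deliver intention-to-treat, and silence about imputation is not in itself a fault. What remains is that the article does fix a population and a method, and the method on its own does not give that population.

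Four stronger readings are tempting, and the documents do not support them.

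- **That the sample size proves a completer analysis was intended.** Inflating for attrition is routine before any analysis, because lost data cost information under all of them. The 105 is not in the article and rests on an unstated ρ and ε.
- **That adverse events tie dropout to arm.** The stopping clause is limited to irreversible events, and it is unclear whether it ends treatment or participation. Nothing says that assessments cease, and the three assessments are scheduled without exception for those who stop treatment. Arm-related dropout is possible but not shown.
- **That 19 participants will be lost.** Nineteen is an expectation under a planning assumption that the article itself calls conservative. Scattered missed visits would raise it and better retention would lower it. The article does not say how many would have a post-intervention value to discard.
- **That the trial loses power.** It does not, against its own plan, since the inflation covers the loss.

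**Conclusion.** The point holds as a conflict between two statements in the same section. Followed as written, the analysis of treatment effects would keep about 105 of 124 randomised participants at the assumed 15% attrition, and it would be reported as intention-to-treat. The damage is to that label and to protection against selective dropout. Whether there would be bias, and in which direction, cannot be told from the article: it requires dropout that is related to outcome and that differs between arms. The conclusion rests on the ANOVA being run on the data as collected, with no imputation beforehand. If a fuller plan specifies imputation, the conflict is resolved and only the article's wording needs to say so.

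**What to change.** Make one of two changes before the analyst learns the allocation.

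1. **Preferred:** replace the repeated-measures ANOVA with a linear mixed model for repeated measures (SPSS MIXED). Outcomes are the post-intervention and follow-up values, with group × visit as the fixed part and baseline score as covariate. Use all available data from all randomised participants as allocated. The model is valid if data are missing at random. A participant with no post-baseline value adds nothing to the contrast, and the report should count such participants by arm.
2. **Alternative:** keep the planned ANOVA but apply multiple imputation first, and state how results are pooled.

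In either case, state that scheduled outcome assessments continue for participants who stop treatment but remain in the study. Reconcile the ambiguous sentence under Withdrawal and adverse events with the three assessments under Outcome measures, so that stopping treatment and leaving the study are told apart. When treatment should be stopped is for the investigators and is not at issue here.

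A sensitivity analysis for departures from missing-at-random and adjustment for hospital are optional; the conflict does not require them. The cost is revised wording and a little more analysis work, in the same software and at visits already scheduled.

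### Covariates are chosen by undefined baseline differences between randomised groups, so the primary model is not fixed in advance and the baseline score becomes a covariate only by chance

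*Protocol article*

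**What the plan says.** The Statistical analysis section of the protocol article sets out three steps.

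- Baseline comparison: "To compare the baseline characteristics of the four groups, one-way ANOVA (or its nonparametric equivalent: Kruskal–Wallis test) or Chi-square tests will be used".
- Covariate choice: "Those relevant variables that show important between-group differences will be entered as covariates for subsequent analysis".
- Model: "multivariate 4 × 3 ANOVA or ANCOVA with repeated measures (mixed design; repeated factor: time; between-subject factor: group) will be used", used for the time effect and the treatment-by-time interaction of each outcome.

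No covariate is named in advance. No threshold is given for an important difference, and nothing says what makes a variable relevant. The only significance level in the article is the 0.05 in the Sample size section, which belongs to the main test.

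The Outcome measures section puts the assessments "at baseline, within 1-week after the completion of intervention, and at a 4-week follow-up". The three time levels of the model therefore include baseline. Assessments are "performed by a blinded assessor in each hospital on three occasions", and the Participants section names two recruiting hospitals. The Randomization and blinding section describes a random sequence, mentions no stratification, and keeps the data analyst blind to allocation.

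**The concern.** Allocation is random, so any baseline difference between groups is due to chance. A test of that difference, or a judgement of its size, does not show whether the variable predicts outcome, and prediction is what makes a covariate useful. The rule selects on imbalance instead.

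Three consequences follow.

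1. The baseline VAS or WOMAC score, a natural prognostic covariate that is already collected, enters as a covariate only if it happens to be imbalanced.
2. Whether the primary model is an ANOVA or an ANCOVA, and with which covariates, is unknown until the baseline data are examined. With both criteria undefined, two analysts could follow the article faithfully and fit different models.
3. If a baseline score is flagged, it becomes a covariate while it is still one of the three repeated responses.

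At stake are precision in a trial with 31 patients per group, and a primary analysis that can be reproduced from the plan.

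**Working it through.** **1. The plan's own figure.** Inputs from the Sample size section: "assuming a small effect size (*f* = 0.15), a significance level (*α*) of 0.05, statistical power of 0.80, and accounting for a 15% attrition rate", and "the total sample size required was 124 participants, evenly distributed across the four groups, i.e., 31 in each group". The correlation between visits is not stated; 0.5 with sphericity is assumed here. For the group-by-time interaction with k = 4 groups and m = 3 times:

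- noncentrality = N × f² × m / (1 − r) = N × 0.0225 × 3 / 0.5
- df1 = (k − 1)(m − 1) = 6; df2 = (N − 4) × 2

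N = 104 gives power 0.799 and N = 105 gives 0.804. Then 105 / 0.85 = 123.5, rounded up to 124 = 4 × 31. The stated total is reproduced on the 6-df interaction.

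**2. How often would a given baseline score not become a covariate?** This depends on what an important difference means, so a range is needed.

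| Assumed meaning | Share of trials in which it is not entered |
|---|---|
| p < 0.05 | 95% |
| p < 0.10 | 90% |
| p < 0.20 | 80% |
| largest pairwise difference above 0.3 SD | about 36% |
| above 0.5 SD | about 79% |
| above 0.8 SD | about 99% |

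The first three rows are 1 minus the threshold, which is exact under randomisation. The last three use the studentized range for four groups of 31; the chances of exceeding 0.3, 0.5 and 0.8 SD are 0.640, 0.206 and 0.011.

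**3. How stable is the covariate set?** If several independent variables were each tested at 0.05, the chance that none is flagged is 0.95² = 90% for two, 0.95⁵ = 77% for five and 0.95¹⁰ = 60% for ten. Real baseline variables are correlated, so these figures are only illustrative.

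**4. Efficiency.** Take unit variance and an equal correlation r between any two visits. The comparator is change from baseline, because baseline is the first time level.

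- One post-treatment visit: change 2(1 − r); ANCOVA 1 − r².
- Mean of the two post-treatment visits: change (1 + r)/2 + 1 − 2r; ANCOVA (1 + r)/2 − r².

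| r (assumed) | One visit: change / ANCOVA | Ratio | Two-visit mean: change / ANCOVA | Ratio |
|---|---|---|---|---|
| 0.3 | 1.40 / 0.91 | 1.54 | 1.05 / 0.56 | 1.88 |
| 0.5 | 1.00 / 0.75 | 1.33 | 0.75 / 0.50 | 1.50 |
| 0.7 | 0.60 / 0.51 | 1.18 | 0.45 / 0.36 | 1.25 |

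These ratios apply to those two contrasts. They are not the gain on the 6-df interaction test, which also contains the comparison between the two post-treatment visits.

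**5. Type I error.** The two-stage rule (ANCOVA if the baseline score is flagged at 0.05, otherwise change from baseline) was simulated at one post-treatment visit. There were 20,000 trials for each correlation, with 26 patients per group and no treatment effect. The score was flagged in 4.7% to 5.1% of trials. Overall type I error was 4.2% to 4.5% against a nominal 5%. Among flagged trials only, the unadjusted change-score test rejected in 12% to 19%.

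**The case against.** The strongest reply is that little harm is done. Baseline is already in the model as the first time level, so the treatment-by-time interaction works on changes from it. Selection uses baseline data, not outcomes, and the analyst is blind to allocation. The rule limits entry to relevant variables. A fuller covariate list may sit in an analysis plan that is not shown.

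Most of this stands, and it rules out several stronger readings that a reader might infer.

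- **That about 95% of such trials lose the baseline covariate.** This holds only if an important difference means p < 0.05, and it applies to one score at a time. The article sets no such threshold.
- **That most trials would run without any use of baseline.** The three-level time factor contradicts this.
- **That standard errors are invalid or false positives inflated.** The simulation shows slightly conservative type I error. Adjusting in flagged trials helps, because leaving them unadjusted gives 12% to 19% rejection.
- **That the analyst may pick the model from the results.** The stated trigger is baseline data and the analyst is blinded. The weakness is the undefined threshold.
- **That hospital or Kellgren-Lawrence grade must be in the model.** No stratification by either is described, so the design does not require it.

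The reply does not rescue the rule itself. The article states how covariates will be chosen, so this is not detail left to another document. Restricting entry to relevant variables does not fix the model while that term is undefined. Working on change is not the same as adjusting for baseline, and it is less efficient at every correlation in the table.

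**Conclusion.** The point holds as a should-fix. The covariate rule selects on chance imbalance with undefined criteria, so the primary model is not fixed in advance and baseline adjustment happens by accident. The share of trials in which a given baseline score would not be entered runs from about 36% to 99% across plausible readings. That spread itself shows that the rule cannot be reproduced from the text.

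The cost is efficiency: a variance ratio of 1.54 to 1.18 at a single visit for correlations of 0.3 to 0.7, and 1.50 for the two-visit mean at 0.5. The correlations are assumptions. The value 0.5 reproduces the sample size but is not stated in the article. The ratios should not be read as a saving in patients on the planned interaction test. There is no evidence here of bias, inflated type I error or a sample-size error.

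**What to change.** In the Statistical analysis section:

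- Delete the rule that enters variables showing baseline differences, and drop baseline significance tests as a way to choose covariates. Baseline characteristics can simply be described by group.
- State that each outcome is analysed at the two post-baseline visits, with its own baseline value as a pre-specified covariate whatever the balance. Baseline is then no longer also a repeated response.
- Name the primary test as the adjusted group effect, either at the post-intervention visit or averaged over both visits, and choose which in advance. This step is essential. Once baseline leaves the response, a group-by-time interaction tests only whether group differences change between the two remaining visits.
- Optionally, add hospital as a pre-specified covariate, since each hospital has its own assessor.

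Cost: no new data and no change to the total of 124. The primary test will no longer be the 4 × 3 interaction on which the Sample size section is based, so that section needs a sentence saying so. The change should be made before any analysis by treatment group.

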#### Secondary outcomes

*Muscle strength*: the manual muscle test (MMT) will be used to test the muscle strength of flexor and extensor in knee and hip.

*Range of Motion (ROM)*: the goniometer will be used to measure the active and passive flexion and extension ROM in hip, knee, and ankle joint.

*Alignment:* the Q angle will be measured via the X-ray.

*Joint space:* the joint space will be quantified by X-ray.

*Cytokines in serum:* TNF-*α*, interleukin-1β (IL-1β), interleukin-15 (IL-15), C1q/tumor necrosis factor-related protein-9 (CTRP9), and interleukin-29 (IL-29), CRP, hs-CRP, MMP-3, MMP-13, HA, NO, MDA, PGE-2.

*Cytokines in synovial fluid:* interleukin-34 (IL-34), interleukin-37 (IL-37), and interleukin-6 (IL-6).

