## Discussion

This trial is poised to conduct a thorough comparative analysis of the impacts of ECHT, PEMF therapy, and their combined application on pain alleviation, functional improvement, and the modulation of blood inflammatory biomarkers in older adults with KOA. The study is meticulously designed to test the central hypothesis that a synergistic approach, integrating both ECHT and PEMF therapies, will induce more pronounced alterations in blood inflammatory biomarkers. This, in turn, is hypothesized to result in superior improvements in pain and functional capabilities compared to either intervention employed in isolation.

The study’s objectives are twofold: (1) to rigorously evaluate whether the integration of ECHT and PEMF therapy can achieve more significant modulation of inflammatory biomarkers, which are pivotal in the pathophysiology of KOA. (2) To determine if this combined therapeutic strategy leads to enhanced clinical outcomes in terms of pain reduction and functional enhancement in the elderly population suffering from KOA.

The implications of this trial are profound, as it seeks to provide evidence-based guidance for intervention strategies tailored to the unique needs of older adults with KOA. By elucidating the potential synergistic effects of ECHT and PEMF therapy on inflammatory pathways, the study aims to contribute to a deeper understanding of the mechanisms underlying pain relief and functional improvement in KOA. This knowledge is critical for advancing the development of personalized treatment plans that are both effective and safe for this vulnerable patient demographic.

Ultimately, the findings of this study will not only inform clinical practice by offering data-driven recommendations but also enrich the scientific discourse on the complex interplay between inflammation, pain, and function in KOA. The pursuit of these insights is essential for advancing the frontiers of OA management and enhancing the quality of life for older adults affected by this debilitating condition.

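### Biomarker change is called the central hypothesis but ranked as a secondary outcome; the marker panel is not fixed, and the stated multiplicity rule does not reach across the 13 serum markers

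*Protocol article*

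**What the plan says.** All references are to the protocol article.

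- **Rank as an outcome.** The Abstract makes pain and functional capacity primary and lists serum cytokines as secondary. Secondary outcomes names 13 serum markers: TNF-α, IL-1β, IL-15, CTRP9, IL-29 and then "CRP, hs-CRP, MMP-3, MMP-13, HA, NO, MDA, PGE-2". Three more are measured in synovial fluid.
- **Rank as a hypothesis.** The Discussion says that the study tests the central hypothesis that combining the therapies "will induce more pronounced alterations in blood inflammatory biomarkers", with better pain and function following from this. Objective (1) is "to rigorously evaluate whether the integration of ECHT and PEMF therapy can achieve more significant modulation of inflammatory biomarkers"; clinical outcomes are objective (2). The Introduction also expects larger molecular changes with the combination than with either therapy alone.
- **Test.** Statistical analysis specifies a 4 × 3 mixed-design model that "will be used to determine the time effect and treatment × time interaction effect for each outcome variable of interest". After a significant result, post-hoc comparisons follow, and "Bonferroni adjustment will be performed in" that post-hoc step.
- **Panel.** Study design lists IL-6 among the serum factors and IL-1 among the ELISA markers. Secondary outcomes puts IL-6 in synovial fluid, omits IL-1, and adds serum IL-15, CTRP9 and IL-29.

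**The concern.** A hypothesis called central needs a rule for deciding whether it was supported. Here it rests on a panel of secondary outcomes, with no deciding marker and no order among them. The multiplicity rule that is written down protects comparisons between arms once a given marker is significant; it does nothing about having 13 markers to choose from. Because two sections list different panels, the choice of markers is open as well.

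At stake is the mechanistic claim. A chance result on one marker could be presented as support for the central hypothesis, and the argument that marker change leads to better pain and function would then rest on it.

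**Working it through.** **1. The plan's own figure.** The article states no family-wise error rate; the figure that can be reproduced is the sample size. Inputs from Sample size: "Employing a 4 (group factor) × 3 (time factor) RM ANOVA framework", f = 0.15, and "a significance level (*α*) of 0.05, statistical power of 0.80, and accounting for a 15% attrition rate". Assumed, because not stated: correlation 0.5 between visits and sphericity. The noncentrality is λ = f²·N·m/(1 − ρ) = 0.0225 × 105 × 3 / 0.5 = 14.175. With 6 and 2 × (105 − 4) = 202 degrees of freedom, power is 0.804 at N = 105. Then 105/0.85 = 123.5, rounded up to 124, or 31 per arm. The plan's figure reproduces. It is based on a single interaction test at 0.05.

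**2. Marker count.** Secondary outcomes gives 13 serum markers. Study design gives 12: CRP, hs-CRP, TNF-α, IL-6, MMP-3, MMP-13, HA, NO, MDA, IL-1β, PGE-2 and IL-1. Ten are common to both, so the two lists together hold 12 + 13 − 10 = 15.

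**3. At least one false interaction among 13.** If the markers are independent and each is tested at 0.05, the chance is 1 − 0.95¹³ = 48.7%. Real markers are correlated, and the article gives no correlation, so a range is needed. The simulation used four arms, three visits, normal data, no true effect and equal correlation between markers. Runs with 26 completers per arm and with 31 per arm agree within one or two percentage points.

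**4. The claim in the Discussion.** The hypothesis is that the combination does better than a single therapy, so a claim must also pass the post-hoc step. The article does not detail that step. It was taken as six pairwise comparisons of change from baseline, each at 0.05/6, at either later visit.

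| False finding on at least one of 13 markers | correlation 0 | 0.5 | 0.8 |
|---|---|---|---|
| Any interaction | 48–49% | 34–36% | 20–21% |
| plus an adjusted difference between any two arms | 37% | 28% | 17% |
| plus combination versus a single therapy, either direction | 18–21% | 14–15% | about 8% |
| plus that difference favouring the combination | 10–13% | 7–8% | 4% |
| plus combination better than both single therapies | under about 1% | under about 1% | under about 1% |

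Ranges within a cell are the spread between runs. The row for results favouring the combination presumes that the favourable direction is fixed in advance for each marker. If one therapy truly works and the other adds nothing, the last row rises to about 3% to 10%.

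**5. Effect of adjusting across markers.** Bonferroni over 13 sets 0.05/13 = 0.00385 per test. Under independence the family-wise rate is then 1 − (1 − 0.00385)¹³ = 4.9%.

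**The case against.** - **The interaction rate is not the error rate of objective (1).** A reader might infer a roughly one-in-three chance of a false claim for the central hypothesis. That does not follow. A significant four-arm interaction can arise from, say, control against ECHT alone and says nothing about the combination. Once the post-hoc step is counted, the risk is at most about half as large, and smaller again when direction counts. One in three also depends on an unstated between-marker correlation near 0.5 to 0.6. This objection stands, and it means that adjusting the interaction tests would target the wrong tests.
- **Multiplicity among secondary outcomes often belongs in the SAP.** True, and the absence of an adjustment would not by itself be a finding in a condensed article. But the article contradicts itself on the rank of the biomarkers, and it states a multiplicity rule that does not cover the claim it calls central. Those two points remain.
- **The rank is overstated.** Objective (1) is numbered so only in the Discussion; the Introduction puts pain and function first, and Study design presents the laboratory work as exploring mechanisms. This is fair as context. That wording does not label the outcomes exploratory, however, and the Discussion points the other way.
- **The 5% level is borrowed.** Statistical analysis gives no level; 0.05 comes from Sample size. The word multivariate there could also mean a joint test, although testing each outcome variable points to separate tests. Both are stated here as assumptions.

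**Conclusion.** The concern holds in a limited form. The article contradicts itself on the rank of the biomarkers and on which markers make up the panel, and its stated Bonferroni step gives no error control across the 13 serum markers. With 5% per test and no true effect, at least one false interaction has a chance of about 20% to 49%. A false difference between the combination and a single therapy has a chance of about 8% to 21% in either direction and about 4% to 13% in favour of the combination. For beating both single therapies it is under about 1% under a complete null. These figures rest on an assumed between-marker correlation of 0.8 to 0, normal data, sphericity and the reading of the post-hoc step given above.

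The documents do not support reading any single significant interaction as confirmation of the central hypothesis, nor extending the point to pain and WOMAC. The primary endpoints are unaffected. The change is worth making because it determines what the trial may claim about mechanism.

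**What to change.** First reconcile the marker lists in Study design and Secondary outcomes: whether IL-6 is a serum or a synovial fluid marker, whether IL-1 is measured, and where IL-15, CTRP9 and IL-29 belong. Then do one of the following.

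- **Exploratory.** Label the biomarker outcomes exploratory in Secondary outcomes and Statistical analysis, and reword the central hypothesis and objective (1) in the Discussion to match, so that no confirmatory biomarker claim is made. The cost is a weaker stated claim.
- **Confirmatory.** Keep the claim, and state in Statistical analysis that it is judged on the combination-versus-ECHT and combination-versus-PEMF contrasts, with Holm adjustment across the fixed serum family, and not on the four-arm interactions. Say whether a marker must show superiority on both contrasts. If it must, the larger of its two p-values enters Holm, giving 13 entries with the current list. If either contrast suffices, all 2 × 13 = 26 enter. The cost is lower power per marker.

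Either route takes a few sentences and no new data.
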